#### Cross-Sectional Clinical Trial: Phase 2 of the Study

Patients with or without visual impairment and/or vestibular dysfunction will be identified based on the results of patients’ diagnosis after the battery of standardized outcome measures has been completed by two independent assessors (audiologist and physiotherapist) during phase 1 of the study. Sixty patients with (visual and/or vestibular dysfunction) identified in phase 1 of the study will be recruited to participate in the second phase of the study and randomly allocated to either Group 1 or Group 2. The study population will include the data of the first 30 patients in each group who participate in the study for all 20 weeks. The two groups of 30 patients in the respective group do not make provision for drop out of participants in the study. If patients leave the study for any reason, they will have to be replaced by another patient. The results of this first battery of tests (phase 1) will serve as the baseline measurements for phase 2 of the study. In phase 2, the researcher will determine the effect of the combination of VRT and VSE integrated with task-specific activities (*n* = 30) as an intervention approach for patients in the sub-acute phase post-stroke compared with patients who will receive task-specific activities (*n* = 30) alone as an intervention approach on their: (a) visual impairments, (b) central vestibular dysfunction, (c) cognitive function, (d) residual oculomotor visual performance, (e) visual–perceptual system, (f) functional balance, (g) ability to modify gait in response to changing task demands, (h) functional ability, and (i) presence of anxiety and/or depression after the intervention period of 2 weeks. The consecutive assessment will be repeated by the two independent assessors after the 2-week intervention period. Twenty weeks after rehabilitation has been terminated, the physiotherapist (independent assessor) will contact all patients who completed phase 2 of the study, to complete the Telephonic-Administered International Physical Activity Questionnaire (IPAQ). The aim will be to determine the effect of the combination of VRT and VSE integrated with task-specific activities for patients in Group 1 (experimental group), compared with patients who will receive task-specific activities alone Group 2 (control group) on patients’ participation activities 20 weeks after rehabilitation has been terminated.

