### Data Management and Analysis

Data of the cross-sectional survey (phase 1 of the study) will be analyzed and reported according to the STROBE checklist. Data of the cross-sectional clinical trial (phase 2 of the study) will be analyzed and reported according to the CONSORT statement. The outcomes measures measuring the clinical outcomes the data summary will make use of descriptive statistics, geometric mean, SD, median, range, and 95% CIs will be used when data conforms to a Gaussian distribution. Results from the two groups will be compared with respect to outcome at 2 weeks, adjusted for baseline values, using analysis of covariance (ANCOVA), using ranks when data are skewed. Data characteristics permitting, groups may also be compared using a mixed-model approach which will indicate the data over all the time points where treatment, time, and treatment–time interaction will be entered into the model, and the treatment–time interaction will be of primary intent. Testing will be done at the 0.05 level of significance.

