#### Limitations of the Study

•Upon completion of the previous study by the authors, a large number of drop out of participants after discharge from various rehabilitation settings in South Africa was observed limited long-term follow-up despite the fact that participants received remuneration for traveling costs and were contacted telephonically on a regular basis. The large loss to follow-up prevented the researcher from determining whether the long-term effect of the treatment was sustained and was regarded as a limitation of the previous study.•Twenty weeks after rehabilitation has been terminated, the physiotherapist (independent assessor) will contact all patients who completed phase 2 of the study, to complete the Telephonic-Administered International Physical Activity Questionnaire (IPAQ) to determine the effect of the combination of VRT and VSE integrated with task-specific activities for patients in Group 1 (experimental group), compared with patients in Group 2 (control group) who will receive task-specific activities alone on their participation activities 20 weeks after rehabilitation has been terminated.

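### The 2-week treatment comparison is restricted to patients who stay in the study for 20 weeks, a condition met after randomisation and after the outcome is measured

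*Protocol article*

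**What the plan says.** All references are to the protocol article.

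- **Who is analysed** (Cross-Sectional Clinical Trial: Phase 2 of the Study). Patients are "randomly allocated to either Group 1 or Group 2". Then: "The study population will include the data of the first 30 patients in each group who participate in the study for all 20 weeks". The next sentences add "The two groups of 30 patients in the respective group do not make provision for drop out of participants in the study" and "If patients leave the study for any reason, they will have to be replaced by another patient".
- **When outcomes are measured** (same section). The clinical battery is repeated after the 2-week intervention. The IPAQ is taken by telephone 20 weeks after rehabilitation ends, when the assessor "will contact all patients who completed phase 2 of the study".
- **What is tested** (Data Management and Analysis). "Results from the two groups will be compared with respect to outcome at 2 weeks", by baseline-adjusted ANCOVA, with a mixed model as an option. On reporting: "Data of the cross-sectional clinical trial (phase 2 of the study) will be analyzed and reported according to the CONSORT statement".
- **What the trial is sized on** (Sample Size). The change in Barthel Index at 2 weeks, on the log10 scale.
- **What is known about loss** (Limitations of the Study). Many participants of the previous study dropped out after discharge: "The large loss to follow-up prevented the researcher from determining whether the long-term effect of the treatment was sustained".

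**The concern.** Staying for 20 weeks is decided after randomisation and after the 2-week outcome is known. A patient with complete baseline and 2-week assessments who dies or cannot be reached months later falls outside the stated population, and another patient takes the place. The groups compared at 2 weeks are then those who stayed, not those who were randomised.

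If the chance of staying depends on how well the patient did, and does so differently by arm, the comparison is biased even when treatment has no effect. Differential retention is conceivable here: the principal investigator treats the whole experimental arm, while site physiotherapists treat the controls. The result also has a consequence, because the Abstract ties staff training to a clinically and statistically significant Barthel Index result.

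The exclusion buys nothing for the 2-week question, since the discarded outcomes have already been observed.

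**Working it through.** **1. Timing.**

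| Step | Time | Needs 20-week participation? |
|---|---|---|
| Baseline battery (phase 1) | before allocation | no |
| Barthel Index and rest of clinical battery | 2 weeks | no |
| ANCOVA between groups | on 2-week values | no |
| Telephone IPAQ | 20 weeks after rehabilitation ends | yes |
| Membership of the stated population | 20 weeks | yes |

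Only the IPAQ analysis needs the condition that defines the whole population.

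**2. The plan's own sample size.** From Sample Size: difference 0.214, SD of change 0.249, 90% power, alpha 0.05.

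n per group = 2 × (1.960 + 1.282)² × 0.249² / 0.214² = 28.5, so 29 (t-test 29.4, so 30). With the SD as 0.179 × √2 = 0.253, n = 30. The stated 30 reproduces as a two-sided figure. Power at 30 per group with SD 0.249:

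0.214 / (0.249 × √(2/30)) − 1.960 = 3.329 − 1.960 = 1.369, giving 91.4% (t-test 90.5%).

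So 30 completers per group give the planned power.

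**3. Observed results set aside.** The protocol gives no loss rate; 10 to 40% is assumed, all after week 2. Filling 60 completers takes 60/(1 − q) randomised patients, and the excess over 60 is discarded. The last column is normal-approximation power if that excess is kept.

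| Loss q | Randomised | 2-week results discarded | Power if kept |
|---|---|---|---|
| 10% | 67 | 7 | 93.9% |
| 20% | 75 | 15 | 96.1% |
| 30% | 86 | 26 | 97.8% |
| 40% | 100 | 40 | 99.0% |

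**4. Bias and type I error, by simulation with no true effect.** Inputs: SD of log10 Barthel 0.179 (Sample Size). Assumed: baseline correlation 0.5 to 0.7, 30% loss by 20 weeks, first 30 stayers per arm analysed by ANCOVA, and logit P(stay) = a + b × (2-week score in SD units). With b = 0.7, the odds of staying double per SD (e^0.7 = 2.0).

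| Dependence of staying on the 2-week score | Bias (log10) | Type I error |
|---|---|---|
| None, or equal in both arms | 0 | about 5% |
| One arm only | 0.02 to 0.03 (0.017 to 0.028) | 8 to 10% |
| Opposite directions | 0.04 to 0.06 (0.037 to 0.056) | 20 to 29% |

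On the Barthel scale from the protocol's starting value of 45, the shift is 45 × (10^bias − 1). The one-arm range is 1.8 to 3.0 points and the opposite-direction range 4.0 to 6.2 points. As shares of the 0.214 effect these are 8 to 13% and 17 to 26%.

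**5. Sensitivity to the assumptions.** A steeper slope of 1 logit per SD, with SD 0.249, 30% loss and an unadjusted t-test, gives bias 0.062 and 17% type I error for one arm, and 0.126 and 55% for opposite directions. The same slope in both arms with 20% against 40% loss gives −0.040 and 10%. With no dependence, or equal dependence and equal loss, type I error is 4.8% and 5.2%. The size is driven by assumptions that the protocol does not supply.

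**The case against.** **It may be only a recruitment target.** The sentence stands in the data collection section beside the replacement rule, and the analysis section sets no 20-week condition. A condensed article may leave analysis sets to a fuller document. This deserves some weight: nowhere is it said outright that a patient lost after week 2 is removed from the ANCOVA. But the sentence speaks of whose data the study population will include, and nothing in the protocol article brings the lost patients back. The CONSORT commitment names no analysis set. The mixed model is optional and would draw on the same population. Telephoning everyone who completed phase 2 settles who is called, not whose 2-week data are used. This is a stated rule, not a silence.

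**Bias is not inevitable.** This stands. Loss unrelated to outcome, or related to it equally in both arms at the same rate, leaves the comparison unbiased. The opposite-direction case is an extreme, and nothing in the protocol points to it.

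**The previous study is weak evidence on loss.** Partly so. No rate is given, and the only 20-week outcome here is a telephone call. But participants of that study were also telephoned regularly and had their travel costs paid.

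**Stronger readings that do not hold.** A reader might infer that the rule leaves the trial underpowered. It does not: leavers are replaced until 30 per group have stayed, and that number carries the stated power. Whether the phase 1 pool can supply enough replacements is a separate question. A reader might also infer that completers beyond the thirtieth are thrown away. With sixty recruited and leavers replaced, no surplus is planned.

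**Conclusion.** The point holds. As written, the rule conditions a 2-week comparison on a later, post-randomisation event and discards 2-week outcomes already observed.

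The loss of observed data follows for anyone who leaves after week 2. It is a loss relative to data in hand, not a shortfall from the planned 90% power. The bias is conditional: it requires retention related to outcome differently by arm, or at different loss rates. Its direction cannot be told from the protocol, so it would be wrong to say that the rule favours the experimental group. The figures in the working illustrate what moderate dependence would do; they do not predict what will happen. The rule should still be changed before analysis, because it touches the comparison on which the trial is sized and its harmlessness cannot be shown in advance.

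**What to change.** In the phase 2 section, replace the sentence that defines the study population with wording to this effect:

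- The 2-week comparison includes all randomised patients in the arm to which they were allocated. It uses every observed 2-week assessment, whether or not the patient is reached later or has been replaced.
- Missing 2-week values are handled by a likelihood-based or imputation method, with a sensitivity analysis to the assumption about why they are missing.
- Being among the first 30 per group to complete 20 weeks is no longer a condition for analysis.
- The 20-week condition applies to the IPAQ analysis only.

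Replacement may continue as a recruitment device, provided that the replaced patient's data stay in the 2-week analysis. The cost is a change of wording and slightly more analysis work. No added visits or assessments are needed.

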**Ethics and dissemination:**

Ethics approval has been obtained from the Ethics Committee of the Faculty of Health Sciences at the University of Pretoria (UP) (374/2015). The study will be submitted as fulfillment for the PhD degree at UP. Dissemination will include submission to peer-reviewed professional journals and presentation at congresses. Training of rehabilitation team members on the integration of VSE and VRT into task-specific activities in rehabilitation will be done if the outcome of the experimental group’s functional performance is clinically and statistically significantly better than the control group on the Barthel Index.

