### Sample Size

The sample size of phases 1 and 2 are interrelated and was calculated simultaneously with the assistance of a statistician. All patients who suffered a stroke and will be admitted at one of the pre-selected rehabilitation hospitals in Pretoria and Johannesburg, Gauteng for rehabilitation in the sub-acute phase will be assessed to determine if they meet the inclusion and exclusion criteria of the study. Recruitment and assessment of patients will be done in each of the rehabilitation centers in a consecutive sequence based on the number of patients in a particular center at a given time until an adequate and representative sample group (*n* = 100) for the trial has been reached. An adequate and representative sample size required for phase 1 of the study was calculated based on a relatively small, but similar study (12). These authors reported the geometric mean and 95% confidence interval (CI) at baseline and the end of each week of the treatment period. The expected geometric mean of the Barthel Index value at onset was 45 (12) and an improvement in the change from baseline at 2 weeks for the combination of VSE integrated with task-specific activities group (experimental group) compared with the task-specific activities group (control group) is 36 which is 0.214 on the logarithmic (base 10) scale. From the reported 95% CI for the geometric mean, a SD of 0.179 on the log scale was calculated. Since a change from baseline of interest, this SD was inflated by a factor (√2 to 0.249). Based on this information, a sample of at least 30 patients per group will have 90% power to detect the clinical relevant change when testing at the 0.05 level of significance. If testing was one-sided (VRT, VSE, and task-specific activities), based on the published results of the previous study (12), a sample of 30 patients per group will be required. Hence, to achieve a sample size of 30 patients per group, the cross-sectional part of the study (phase 1) will need to enrol at least 100 patients in the sub-acute phase. Prevalence of visual impairments and central vestibular dysfunction will be of interest. As the latter is expected to be in excess of 70% the above sample size is adequate to estimate the prevalence’s to an accuracy within 10%. One hundred patients who meet the eligibility criteria and will give written informed consent to participate in the study will therefore be included in phase 1 of the trial.

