### Data Collection Procedure

#### Cross-Sectional Survey: Phase 1 of the Study

One hundred (*n* = 100) patients, who meet the eligibility criteria, in the research settings will be recruited for possible participation in the study. Data collection in phase 1 will be done at each of the research settings for an estimated period of 4 weeks/rehabilitation setting. Each patient who meets the eligible criteria for phase 1 in a particular setting and who will give informed consent after a thorough explanation of what the study will entail will be included into the study and undergo the battery of audiological and physiotherapy assessment procedures (Table 1). The patients will also be informed that participation in the trial is voluntary and they are free from undue coercion. In this study, the International Classification of Functioning, Disability and Health (ICF) (25) is used as the model of disablement within which the patients’ levels of impairment, functional activity, and participation will be determined and documented. Collection of comprehensive demographic information relating to age, gender, race, affected side post-stroke, dominant side prior to stroke, stroke type, type of residence, level of education, and type of work will be collected from patients. Thereafter, an audiologist will assess (a) visual acuity (static and dynamic), (b) nystagmus, (c) saccadic eye movements, (d) smooth pursuit eye movements, (e) vestibulo-ocular reflex, and (f) saccular, utricular, and vestibular nerve function. A physiotherapist who is not involved in the treatment of these patients will assess (1) cognitive function, (2) residual oculomotor visual performance, (3) visual–perceptual system, (4) functional balance, (5) gait, (6) functional ability, and (7) presence of anxiety and/or depression in these patients. If a specific eye condition or eye disease is suspected, the patient will be referred to an ophthalmologist for ophthalmologic assessment and management. The battery of valid and standardized outcome measures that will be completed by a qualified audiologist and physiotherapist (who will not be involved in the allocation of the patients to the experimental and control groups nor the intervention) is summarized in Table 1. The qualified audiologist and physiotherapist will complete the battery of outcome measures over a 2-day period to minimize possible performance fluctuations due to fatigue as result of the lengthy test protocol.

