Patients will receive intervention daily for a period of 2 weeks. The period of intervention consisting of 2 weeks was selected due to the fact that patients are on average admitted to a private rehabilitation setting post-stroke for a period of 2 weeks. The intervention period of 2 weeks were further decided upon because results from a previous study (12) demonstrated a statistically significant (*p* = 0.02) difference between Group 1 and Group 2 after 2 weeks intervention (12). Any adverse effects within the period of 20 weeks will be documented.

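### The 2-week comparison is restricted to patients who stay for all 20 weeks, with leavers replaced, although only the 20-week telephone questionnaire needs that follow-up

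*Protocol article*

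**What the plan says.** The section Cross-Sectional Clinical Trial: Phase 2 of the Study first allocates sixty patients at random and then defines who counts: "The study population will include the data of the first 30 patients in each group who participate in the study for all 20 weeks". It makes no allowance for drop-out and adds: "If patients leave the study for any reason, they will have to be replaced by another patient". No other section gives a separate population for any outcome.

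The analysis is set for an earlier time. Data Management and Analysis states: "Results from the two groups will be compared with respect to outcome at 2 weeks, adjusted for baseline values, using analysis of covariance (ANCOVA"), with ranks if the data are skewed. By Table 1 and the phase 2 section, every clinical outcome other than physical activity is reassessed after the 2-week intervention. Only the telephone IPAQ is collected 20 weeks after rehabilitation ends.

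The Sample Size section rests on the Barthel Index at 2 weeks: a difference of 0.214 and an SD of 0.249 on the log10 scale, 30 per group, 90% power. The abstract (Ethics and dissemination) makes staff training depend on whether the experimental group's "functional performance is clinically and statistically significantly better than the control group on the Barthel Index".

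**The concern.** Membership of the 2-week comparison depends on something that happens after the 2-week value has been recorded and that the comparison does not use. Randomisation makes the two groups of randomised patients comparable. It does not do so for the two groups of patients who go on to take part until week 20. Replacement restores the count of 30 but not the comparability, because the replacements must also stay to be counted.

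The arms could differ in who stays. The principal investigator treats the whole experimental group, while centre physiotherapists treat the control group. That makes unequal leaving plausible; nothing in the protocol shows that it will occur. At stake is the result on which the training decision rests.

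**Working it through.** **1. The plan's own figure.** Inputs from Sample Size: difference 0.214, SD 0.249, level 0.05, power 0.90.

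n per group = 2 × (1.960 + 1.282)² × (0.249 / 0.214)² = 2 × 10.51 × 1.354 = 28.5, so 29 by the normal approximation and 30 by the exact t calculation, two-sided. Power with 30 per group is 0.905 (t) or 0.914 (normal). The stated 30 reproduces. (0.179 × √2 is 0.253 rather than 0.249; that gives 30 or 31 per group and does not affect this point.) The calculation asks for 30 patients per group with a 2-week value. Nothing in it needs participation to week 20.

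**2. The rule against the timeline.**
- Barthel Index and the other clinical outcomes: baseline and after the 2-week intervention.
- IPAQ comparison between groups: 20 weeks after rehabilitation ends.
- Population for both: the first 30 per group who take part for all 20 weeks.

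A patient who is randomised, treated, measured at 2 weeks and then withdraws in week 8 has complete data for the 2-week ANCOVA. Under the stated population that patient is left out and another takes the place.

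**3. When this biases the comparison.** In a simulation with no true effect (SD 0.249, first 30 stayers per arm, 4,000 runs per setting, unadjusted t-test at 5%), the log-odds of leaving changed by 1 per SD of the 2-week change wherever leaving was outcome-related. All leaving rates are assumed.

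| Assumed leaving | Bias (log10) | Rejection rate |
|---|---|---|
| 30% in both arms, unrelated to outcome | about 0 | 5.0% |
| 30% in both arms, related to poor change in both | about 0 | 5.4% |
| 30% against 10%, related to poor change in both | 0.040 | 10.3% |
| 20% in both arms, related in one arm only | 0.042 | 10.5% |
| 30% in both arms, related in one arm only | 0.064 | 17.6% |

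The first two rows show the condition: bias needs a difference between the arms in how leaving relates to outcome.

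**4. A hypothetical scale.** If leavers in one arm differ from stayers by 0.5 to 1 SD, the shift in that arm's mean is the share replaced × the difference in SD × 0.249.
- 5 of 35 replaced: 5/35 × 0.5 × 0.249 = 0.018, to 5/35 × 1 × 0.249 = 0.036. Against 0.214 this is 8% to 17%.
- 10 of 40 replaced: 10/40 × 0.5 × 0.249 = 0.031, to 10/40 × 1 × 0.249 = 0.062. Against 0.214 this is 15% to 29%.

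With no true effect and 30 per group, a two-sided 5% t-test would reject in 5.9% to 8.5% and 7.6% to 15.9% of trials. The shares and differences are assumptions, not estimates for this trial.

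**5. Power if leavers are kept.** Suppose enough patients are randomised to have 30 per group at week 20. For assumed losses of 10%, 20%, 30% and 40%, that means 34, 38, 43 and 50 per group (30 / (1 − loss), rounded up). If all have 2-week values, power at 2 weeks is 94.3%, 96.3%, 97.9% and 99.0% (normal approximation, against 91.4% for 30 per group).

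**The case against.** The strongest reply is about wording. Ethics Considerations and Dissemination uses leaving the study for voluntary withdrawal, and the phase 2 section has the assessor telephone all who completed phase 2, which can be read as phase 2 ending before the call. A missed call is not expressly called leaving. This lowers the certainty about patients who merely cannot be reached. It does not remove the rule: the population sentence says all 20 weeks, so at best the two sentences are in tension. The commitment to CONSORT in Data Management and Analysis is general and does not displace an explicit population.

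Three stronger readings are tempting, and the documents do not support them.
- A reader might infer that about 90% of departures will come after the 2-week measurement. The timeline gives 20/22 = 91%, or 18/20 = 90%, but that is a share of calendar time, not of departures.
- A reader might carry over the earlier study, of which Limitations of the Study says: "The large loss to follow-up prevented the researcher from determining whether the long-term effect of the treatment was sustained". That loss came after discharge, despite paid travel and regular telephone contact. Here the late contact is one telephone questionnaire, and no rate is given. The passage shows that late loss is a known problem for this team, not how large it will be here.
- A reader might add early discharge, since "patients are on average admitted to a private rehabilitation setting post-stroke for a period of 2 weeks". The protocol does not equate discharge with leaving the study and gives no stay for public settings, so this adds nothing firm.

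It is also fair that the rejection rates above come from an unadjusted test. The planned ANCOVA would remove selection that acts through the baseline value.

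**Conclusion.** The point holds as a stated selection rule applied after randomisation, not as a demonstrated bias. As written, a patient with a valid 2-week value who does not take part to week 20 is excluded from the 2-week comparison and replaced. The result is biased if those who leave differ in outcome between the arms. If leaving is unrelated to outcome, or similar in both arms, the effect is about nil. Neither the share of patients affected nor the direction can be derived from the documents, and every bias or error-rate figure above is hypothetical. The rule brings no gain in power at 2 weeks. It should be changed, because the flaw lies in the protocol's own wording, bears on the result that decides training, and is easily removed.

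**What to change.** Amend the phase 2 population and replacement wording as follows.
- Analyse every randomised patient with a 2-week value in the allocated group, by the planned ANCOVA, whatever happens afterwards.
- Do not let later departure or replacement remove anyone from that set. If extra patients are randomised to reach 30 per group at 20 weeks, keep both the leavers and the added patients in the 2-week analysis.
- Report by group how many randomised patients lack a 2-week value.
- Use participation to 20 weeks to define the IPAQ analysis set only.

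The cost is protocol wording. Group sizes at 2 weeks may be slightly unequal or above 30, with no loss of power. The change requires no new fixed sample size and no added visits.

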##### Habituation Exercises

The purpose of habituation exercises is to facilitate a reduction in symptoms through repetitive exposure and practice of a movement that provokes the symptoms experienced by the patient. The aim of habituation exercises is to “de-sensitize” the patient and to improve motion-induced dizziness or vertigo (18, 50, 51). Positions and movements may include moving from sitting to lying in supine, rolling from supine to left side lying, rolling from supine to right side lying, moving from supine to sitting, moving from sitting to left and right Dix–Hallpike position, return to sitting from the Dix–Hallpike position, horizontal and vertical movement of the head and turning 180° to the left and right (51).

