##### Improve an Individual’s Balance and Postural Control

A comprehensive exercise program includes higher-balance activities that are practiced under supervision of a physiotherapist. Standing and walking exercises are progressed by changing the patients’ base of support and speed at which activities are performed (50). Progression to dual-task activities is incorporated within safety limits as the patients’ postural control (observed as improved functional ability) improves.

The principal investigator will treat all patients in the experimental group within the rehabilitation hospital settings and will therefore be aware of participant allocation. Due to the fact that rehabilitation is a multidisciplinary team approach, the patients who participate in the clinical trial will continue to be treated by other members of the multidisciplinary team, namely, the occupational therapist, the speech and language therapist, social worker, and psychologist as it is customary in the relevant rehabilitation hospital settings.

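### The 20-week adverse-effect window has no start point and cannot span the at least 22 weeks from first treatment to the last call, and harms in patients who leave may be lost

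*Protocol article*

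**What the plan says.** All of the following stands in the protocol article, mostly under Cross-Sectional Clinical Trial: Phase 2 of the Study.

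- **Harms:** "Any adverse effects within the period of 20 weeks will be documented". No start or end point is given.
- **Treatment:** "Patients will receive intervention daily for a period of 2 weeks".
- **First contact after treatment:** "The consecutive assessment will be repeated by the two independent assessors after the 2-week intervention period".
- **Last contact:** "Twenty weeks after rehabilitation has been terminated, the physiotherapist (independent assessor) will contact all patients who completed phase 2 of the study". Its stated purpose is the telephone physical activity questionnaire (IPAQ).
- **Whose data are kept:** "The study population will include the data of the first 30 patients in each group who participate in the study for all 20 weeks". A patient who leaves for any reason is to be replaced, and the two groups of 30 contain no allowance for dropout.
- **Who delivers treatment:** "The principal investigator will treat all patients in the experimental group" and so knows the allocation (Improve an Individual's Balance and Postural Control). Centre physiotherapists treat the control group (Control Group). The audiologist and the physiotherapist who assess outcomes are blinded (Quality Control).
- **Nature of the added therapy:** the purpose of the habituation exercises is to "facilitate a reduction in symptoms through repetitive exposure and practice of a movement that provokes the symptoms experienced by the patient" (Habituation Exercises).
- **Earlier experience:** in the authors' previous study, "The large loss to follow-up prevented the researcher from determining whether the long-term effect of the treatment was sustained" (Limitations of the Study).

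**The concern.** Two statements about harms do not fit the rest of the schedule.

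First, a window of 20 weeks is set against a course that lasts longer than 20 weeks. Depending on where counting starts, site staff could reasonably leave out either the weeks in which the exercises are given or the last weeks before the final call.

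Second, the promise to document any adverse effects sits beside a rule that keeps only the data of patients who stay. A patient who stops because of a fall or vertigo would be replaced, would not be on the stated call list, and would fall outside the stated study population.

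This matters because part of the added therapy provokes symptoms on purpose. The only safety support cited, under Ethics Considerations and Dissemination, is a study of visual scanning with task-specific activities. No safety figure is given there for vestibular rehabilitation or for the combination. The article plans to train staff if the result is favourable and to offer the combined treatment to control patients, so readers will look to this trial's harms record.

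**Working it through.** **Step 1. The length of the course.**

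Inputs: intervention 2 weeks; call 20 weeks after rehabilitation ends (both from the Phase 2 section).

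First treatment to call = 2 + 20 = 22 weeks. This is a minimum, because the call is timed from the end of rehabilitation, which may come later than the end of the 2-week intervention.

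The article's figure of 20 weeks is reproduced only as the part after rehabilitation, not as the whole course.

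**Step 2. Where a 20-week window can lie.**

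| Window starts at | Weeks covered | Left out |
|---|---|---|
| First treatment | 0 to 20 | At least the 22 − 20 = 2 weeks before the call |
| End of rehabilitation (taken as week 2) | 2 to 22 | The 2 treatment weeks |

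No placement of 20 weeks covers all 22.

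**Step 3. The harms sentence beside the data rules.**

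- The harms sentence covers any adverse effects. It is not limited to completers or to one group.
- The study-population sentence keeps the data of the first 30 per group who stay for all 20 weeks.
- The replacement sentence applies whatever the reason for leaving, so it includes leaving because of harm.
- The call is directed to those who completed phase 2, and its only stated content is the IPAQ.

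The first statement and the other three can be followed together only if someone decides whether adverse effects in replaced patients are kept and reported. The article does not settle that.

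**Step 4. How much could be lost.**

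The documents give no dropout rate and no event rate, so what follows is an illustration over assumed values. Let *d* be the share of randomised patients who leave, and *r* the event risk in leavers divided by that in completers. Suppose that no leaver's events are counted.

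- Leavers behind 60 completers = 60/(1 − *d*) − 60, with the total rounded up to whole patients.
- Share of affected patients missed = *dr* / [(1 − *d*) + *dr*].

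| *d* (assumed) | Leavers | Missed, *r* = 1 | Missed, *r* = 2 |
|---|---|---|---|
| 10% | 7 | 10% | 18% |
| 20% | 15 | 20% | 33% |
| 30% | 26 | 30% | 46% |
| 40% | 40 | 40% | 57% |

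Example for *d* = 40%, *r* = 2: 0.8 / (0.6 + 0.8) = 57%.

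The bottom row would need 60 + 40 = 100 randomised patients, as many as the whole planned phase 1 sample, so it marks an outer limit. The table shows what is possible if leavers' events go uncounted. It does not estimate what will happen.

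**The case against.** The strongest reply has four parts.

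**Twenty weeks is shorthand.** The exclusion criteria and the study-population sentence both use 20 weeks for the whole of participation, and the harms sentence closes a paragraph about the 2-week intervention. On that reading treatment is covered, and only about 2 weeks at the end are in doubt. This is plausible, and it makes the omission of the treatment weeks the less likely reading. It does not remove the mismatch between 20 and at least 22 weeks.

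**An article may leave safety procedures to the full protocol.** This stands. A reader might infer that nobody contacts patients between the 2-week assessment and the call, or that leavers are never reached. The documents do not say so. The article describes no contact in that interval, which is not a statement that none is planned. Event lists, definitions and the choice between adverse effect and adverse event are likewise details that an article may omit.

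**Events during treatment would be seen.** Patients are treated daily by physiotherapists in both groups, alongside a multidisciplinary team, and the balance work is supervised. This also stands. A reader might infer that harms of the new therapy will be under-counted. That is not shown: different people treat the two groups, so recording may differ, but the documents do not show in which direction.

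**Safety comparison is not a stated aim.** The listed objectives contain none, and the abstract ties staff training to superiority on the Barthel Index. This lowers the severity. It does not excuse a harms sentence that conflicts with the schedule and the data rules printed beside it.

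**Conclusion.** The point holds as a should-fix clarification that affects what enters the harms record.

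Two things follow from the stated text. A 20-week window without a start point cannot cover a course of at least 22 weeks; the shortfall is at least 2 weeks, at one end or the other. And the rules on study population, replacement and the call leave patients who stop early outside the stated follow-up and the stated data, while the harms sentence promises any adverse effects.

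The size of any loss rests entirely on assumed dropout and event risks. Across the ranges shown it runs from 10% to 57% of affected patients, and only if leavers' events are in fact not counted. Neither an under-count nor a bias towards one group is demonstrated.

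**What to change.** 1. Define the window as running from first study treatment to the final call, at least 22 weeks, and reconcile the reference to all 20 weeks in the study-population sentence with it.
2. Have the blinded physiotherapist ask the same adverse-event questions in both groups at the existing 2-week assessment and at the existing call 20 weeks after rehabilitation ends.
3. Attempt that call for every randomised patient who has not withdrawn consent to contact, including those who were replaced. This respects the right to leave set out under Ethics Considerations and Dissemination.
4. Record the reason for leaving.
5. Report adverse events by group for all randomised patients who started treatment.

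The cost is protocol wording, a few minutes at two contacts that already exist, and a few extra calls. No new visits or staff are needed. It should be settled before enrolment, because events in patients who have left may not be recoverable later.
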